### Attitudinal Change and its Effects on Behavior

The theory of reasoned action and theory of planned behavior are the most frequently tested models of attitude-behavior relations. Both models view a particular behavior as a function of salient information, or beliefs, relevant to that behavior [17]. Beliefs about the positive outcomes of a behavior lead people to favor and engage in that behavior, while beliefs about its undesirable consequences hinder them from doing so. Research also supports the correlation between attitudinal change and behavioral change [18]. Hence, interventions aimed at changing attitudes towards alcohol use have the potential to induce simultaneous changes in drinking behavior. The aims of this study are to test the effectiveness of an online quiz competition in changing adolescents’ alcohol-related attitudes and behavior and to explore the feasibility of using Internet viral marketing to reach a significant number of adolescents.

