## Methods

### Study Design

The proposed study will consist of a cluster randomized controlled trial on the effectiveness of an Internet quiz competition in promoting healthy attitudes and behaviors towards alcohol use among adolescents. As the intervention website could be referred by participants, cluster randomization, instead of individual-level randomization, is chosen to minimize treatment contamination. The study will employ an Internet viral marketing strategy to maximize sample size. In total, 24 schools (6552 Grade 7-9 students) will be recruited with the collaboration of our community partners such as the Tung Wah Group of Hospitals. Considering that the average number of students in one secondary school class is 35 and that there are four classes in each grade, a total of 10,080 students (24×3×4×35) will be reached. Assuming a response rate of 65%, the number of effective campaign starters will be 6552. Students who cannot comprehend basic Chinese and Cantonese will be excluded.

Half the schools will be randomized for the Internet quiz competition campaign (intervention arm) and half will be randomized for an information package (control arm). Students in the intervention group will be given the opportunity to take part in the online quiz competition and refer others to join the campaign, whereas those in the control group will receive an electronic information package containing comparable information as the intervention arm. All participating students’ demographics and change in attitude and behavior will be measured by questionnaire surveys before intervention, within 1 month, and between 2-3 months after intervention. A longer-term follow-up (12 months after intervention) will also be attempted if schools are willing to commit and resources allow. Weblog data will also be collected from website servers for subsequent analysis of the effectiveness of the Internet viral marketing strategy. Figure 1 is a flowchart of the proposed study.

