### Campaign Design

Participants of the campaign will receive a referral code from those who refer them to the online quiz website; starters of the campaigns will receive the code directly from the research team. These referral codes, sets of 8-digit numbers, will be unique to each user and used to track the referral process. During registration, participants will be asked to provide basic demographic information and their referral code. After registration, their baseline attitudes and behavior will be assessed using the Alcohol Attitudes and Behavior survey.

The campaign will last for 30 days, starting from the day of the school promotion session. The aim of the competition from the participants’ perspective will be to obtain the highest score possible to win a prize. They will have two ways of doing so.

The first way will be to answer the online quiz questions. The po­ints gained in this way will constitute the “answer score.” Alcohol-related multiple-choice questions will be presented on the webpage one by one in random non-repeated order. Each correct answer will result in 10 points being awarded to the user’s account. Giving an incorrect answer or skipping a question will not result in any points being deducted. Users will be shown the correct answer immediately after they have chosen their own. The purpose of this design is to promote correct alcohol-related knowledge and attitudes.

The second way of accruing points to obtain a high score will be to make referrals, a step designed to enhance the effectiveness of the Internet viral marketing strategy. Upon a successful referral, the referrer will receive all of the answer scores of their direct referrals (which will constitute their “referral score”). To minimize the chance of self-referrals, users will receive no points from making a successful referral. Furthermore, to ensure campaign competitiveness, the referral scores of lower-level users will not be added to starters’ accounts. The answer score and referral score will be summed into a total score that will be used for prize distribution. Figure 2 illustrates the point system.

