### Incentive Scheme

An incentive scheme will be used to encourage active participation. The 10 highest scorers in each school will receive cash coupons of different values. Table 1 presents the detailed incentive scheme for each school.

**Table 1 table1:** Prizes for the campaign winners in each school.

Rank of total score	Total number of prizes	Prize for each school	Value (HK$)
1	1	Cash coupon	500
2-3	2	Cash coupon	300
4-10	7	Cash coupon	200
Total			2500

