### Control Arm: Information Package

A comprehensive package on alcohol-related information will be distributed to all students in the control arm. The information package will contain both printed promotional leaflets from the Department of Health and an electronic guideline for understanding alcohol-related information. The electronic guideline sent through the school intranet system would serve as a unidirectional knowledge transfer medium, which would include a brief summary of the most recent research regarding alcohol and a comprehensive list of relevant website and information sources. We will use these relevant websites and information sources in setting the quiz questions for the intervention arm. As a result, both intervention and control arms could have comparable accessibility to alcohol-related information and the sole contrast between the two groups would be the method of presentation (interactive online quiz competition vs unidirectional information package).

Due to the referral nature of the Internet campaign, it is possible that a small portion of students in the control group school would be referred to participate in the quiz competition, which could in turn dilute the effect size estimate. As a result, we will ask the students in the control group in the postintervention survey whether they have participated in the Internet quiz competition campaign and exclude those who participate in subsequent data analysis.

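### Schools are randomised to limit contamination by referral, yet the scoring rule rewards referrals regardless of school or arm, and the stated response to control-school crossover comes only after exposure

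*Protocol article*

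**What the plan says.** The Study Design section gives one reason for randomising schools: "As the intervention website could be referred by participants, cluster randomization, instead of individual-level randomization, is chosen to minimize treatment contamination". The trial also has a second aim, "to explore the feasibility of using Internet viral marketing to reach a significant number of adolescents", and Study Design adds: "The study will employ an Internet viral marketing strategy to maximize sample size".

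Under Campaign Design, a student who brings in a new player is rewarded through that player's results: "the referrer will receive all of the answer scores of their direct referrals". The act of referring pays nothing in itself ("To minimize the chance of self-referrals, users will receive no points from making a successful referral"). Answer score and referral score are added together, and the total decides the prizes. Under Incentive Scheme, "The 10 highest scorers in each school will receive cash coupons of different values", worth HK$200 to HK$500 each. No sentence restricts the referral score to recruits from the referrer's own school or from schools outside the control arm. Registration is described as asking for basic demographics and a referral code.

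The Control Arm section states the consequence: "it is possible that a small portion of students in the control group school would be referred to participate in the quiz competition". It says that this could dilute the effect estimate. Its response is to ask control students in the postintervention survey whether they took part, and to leave out of the analysis those who did.

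**The concern.** The clusters protect the contrast only if the intervention stays inside the intervention schools. The referral score works against that. A control-school recruit is worth as much to the referrer as any other recruit, and is worth more the more quiz questions he or she answers correctly. The incentive therefore grows with the exposure that the design is meant to prevent.

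The stated response cannot undo this. It acts once exposure has happened. It depends on students reporting that they took part, so it can miss crossovers. It also removes students who chose to join from the control arm, with no matching removal in the intervention arm. Crossovers left in the analysis pull the control mean towards the intervention mean. Crossovers taken out leave a control arm that is no longer the one randomised. Either way the estimate for the primary attitude outcome can be biased, although the exposure could be largely prevented at registration.

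**Working it through.** **Inputs.** From Power Analysis: difference 0.5 SD, significance level .05 (two-sided assumed), power 80%, unclustered total 128, ICC 0.092, cluster size 3 × 4 × 35 = 420, inflated total 5063. From Study Design: 24 schools, 1:1 allocation, 6552 starters at a 65% response, so 6552 / 24 = 273 per school. The share of control students who cross over is not given anywhere; the values below are assumptions.

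**The plan's own figure.** A two-sample *t* test with d = 0.5 needs 127.5, so 128 in total. The design effect is 1 + (420 − 1) × 0.092 = 39.548, and 128 × 39.548 = 5062.1, against 5063 stated. The figure reproduces within rounding.

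**Dilution.** Let c be the share of analysed control students who took the quiz, because they were kept or did not report it, and suppose they gain the full effect. The expected contrast is 0.5 × (1 − c).

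| c (assumed) | Expected contrast (SD) |
|---|---|
| 5% | 0.475 |
| 10% | 0.45 |
| 20% | 0.40 |

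**Exclusion.** Now let c be the share of control students excluded, and D the difference in mean attitude, in SD, between those who join and those who do not. The full control mean equals the non-joiners' mean plus c × D, so dropping joiners shifts the control mean by c × D.

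| c (assumed) | D (assumed) | Shift (SD) | Share of 0.5 SD |
|---|---|---|---|
| 5% | 0.5 | 0.025 | 5% |
| 10% | 0.25 | 0.025 | 5% |
| 10% | 0.5 | 0.05 | 10% |
| 20% | 0.5 | 0.10 | 20% |

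The direction depends on whether joiners start out more or less favourable to alcohol, which the documents do not say. If only some crossovers report it, dilution and exclusion bias act together.

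**Power, for comparison.** With 273 per school the design effect is 1 + 272 × 0.092 = 26.024. With 12 schools (3276 students) per arm, the standard error is √(2 × 26.024 / 3276) = 0.126 SD. Under dilution only:

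| c (assumed) | Power, normal | Power, *t* on 22 df |
|---|---|---|
| 0 | 97.8% | 96.6% |
| 10% | 94.6% | 92.7% |
| 20% | 88.8% | 85.8% |
| 30% | 79.3% | 75.6% |

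Power falls below 80% at c of about 29% (normal) or 26% (*t*). Setting the plan's 5063 against 6552 gives a tighter limit: 5063 / (1 − c)² = 6552 at c of about 12%. That limit uses 420 per school, which does not match the 65% response, so the table is the fairer guide.

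**The case against.** The strongest reply is that this is a disclosed trade-off between two stated aims. Allocation by school is itself a protection. Briefings, demonstrations, brochures and posters are confined to intervention schools. The act of referral earns no points, and referral scores of lower-level users do not pass up to starters. The server records every referral code, so crossovers could be traced beyond self-report if school is recorded. The article is also a condensed account, and its list of website changes is given only as examples, so a registration check may exist in a fuller document. All of this stands, and it rules out reading the text as an unnoticed contradiction or as proof that no barrier exists. It does not remove the point: the article itself expects that control students can be referred in, states no limit on the reward for doing so, and fixes a remedy that follows exposure.

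Four stronger readings are tempting, and the documents do not support them.

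- A reader might infer heavy contamination from the eightfold growth in the antismoking pilot. That figure is total growth in another campaign and says nothing about the share of control-school students reached.
- A reader might infer that control schools are the natural targets for referral. On the Study Design figures, 12 × 420 = 5040 students are eligible in intervention schools and 65%, or 3276, start, which leaves 1764 eligible non-starters there. Siblings, other grades and non-trial schools are also open. The community partners are plural, so one shared network cannot be assumed.
- A reader might take the dilution figures as the expected result of the planned analysis. They apply only to crossovers who are kept or unreported, because the plan excludes those who report.
- A reader might conclude that the trial loses its power. Modest crossover does not do that.

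**Conclusion.** The point holds as a design weakness that should be corrected: the reward structure works against the reason given for randomising schools, and the stated remedy trades dilution for one-sided selection. Its size cannot be fixed from the documents, which describe the affected portion only as small and give no figure. At an assumed 10% crossover, the estimate moves by about 0.05 SD on a 0.5 SD target, either by dilution (full effect in crossovers who stay in the analysis) or by exclusion (joiners differing by 0.5 SD). At 20% the movement is about 0.10 SD on the same assumptions. The exclusion shift can go in either direction. The harm is mainly bias in the effect estimate; with 273 respondents per school, power stays above 80% until roughly a quarter of analysed control students have taken the quiz with full effect.

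**What to change.** 1. Record school at registration. Prizes ranked within each school already require it.
2. Award no referral score for registrants from control schools.
3. Defer quiz access for those registrants until their school has completed the 2-3 month survey, or the 12-month survey where the school has agreed to it.
4. Log attempted control-school registrations with their referral codes, and report them as part of reach.
5. Identify crossovers from the server log, not from self-report alone.

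The technical cost is small, because the site is already being modified, including to prevent duplicate registrations. There are two real downsides. A deferred control student cannot refer others during the 30-day campaign, so onward chains are cut and the number of successful referrals per participant is slightly understated; the report should say so. A self-reported school can also be misreported, which would hide a crossover, so it should be checked against school lists where possible.

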**Figure 2 figure2:**
[figure not shown]
Example of the point system.

### Campaign Website and Quiz Questions

The campaign website will be based on our previous Internet viral marketing campaign, which has shown satisfactory user acceptance [16]. We will make necessary modifications such as enhancing the user interface and preventing duplicate registrations for our study.

Setting the quiz questions will be guided by the Elaboration Likelihood Model (ELM) of persuasion. The quiz questions will be designed by youth volunteers to convey accurate and interesting facts based on international and local sources such as World Health Organization and Hong Kong Department of Health reports and research articles from peer-reviewed journals. The questions will be concrete, specific, and of personal relevance to the participants so that they will be more likely to adopt a “central path” of message processing, which the ELM predicts will induce a more sustainable effect [22]. An experienced clinician and a research assistant will examine every set of 100 questions and discuss them with the question setters to ensure language accuracy and information reliability. This process will be repeated until a total of 1000 quiz questions are generated. Finally, all of the questions will be proofread, refined, and approved by a local alcohol research team from the School of Public Health, University of Hong Kong.

### Incentive Scheme

An incentive scheme will be used to encourage active participation. The 10 highest scorers in each school will receive cash coupons of different values. Table 1 presents the detailed incentive scheme for each school.

**Table 1 table1:** Prizes for the campaign winners in each school.

Rank of total score	Total number of prizes	Prize for each school	Value (HK$)
1	1	Cash coupon	500
2-3	2	Cash coupon	300
4-10	7	Cash coupon	200
Total			2500

### Control Arm: Information Package

A comprehensive package on alcohol-related information will be distributed to all students in the control arm. The information package will contain both printed promotional leaflets from the Department of Health and an electronic guideline for understanding alcohol-related information. The electronic guideline sent through the school intranet system would serve as a unidirectional knowledge transfer medium, which would include a brief summary of the most recent research regarding alcohol and a comprehensive list of relevant website and information sources. We will use these relevant websites and information sources in setting the quiz questions for the intervention arm. As a result, both intervention and control arms could have comparable accessibility to alcohol-related information and the sole contrast between the two groups would be the method of presentation (interactive online quiz competition vs unidirectional information package).

Due to the referral nature of the Internet campaign, it is possible that a small portion of students in the control group school would be referred to participate in the quiz competition, which could in turn dilute the effect size estimate. As a result, we will ask the students in the control group in the postintervention survey whether they have participated in the Internet quiz competition campaign and exclude those who participate in subsequent data analysis.

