### Intervention Arm: Internet Quiz Competition Campaign

The intervention is designed based on the Theory of Planned Behavior. Participants will gain alcohol-related knowledge through the participation of the intervention, which would in turn alter their attitude concerning drinking and alcohol use. According to the Theory of Planned Behavior, such knowledge and attitude improvement would reduce participants’ intention to drink and thus change or prevent their drinking behavior [21]. To promote the intervention, we will conduct a briefing session and a demonstration session for all eligible students in participating schools in the intervention arm. Campaign promotion brochures and posters will be distributed within those schools.

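### The arms differ in more than method of presentation, so the trial can test the whole campaign but cannot isolate the interactive format

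*Protocol article*

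**What the plan says.** In Control Arm: Information Package, the article reasons that both arms draw on the same information, and concludes that "the sole contrast between the two groups would be the method of presentation (interactive online quiz competition vs unidirectional information package". The ground given for this is that "We will use these relevant websites and information sources in setting the quiz questions for the intervention arm". The control content is described in the same section: "The information package will contain both printed promotional leaflets from the Department of Health and an electronic guideline for understanding alcohol-related information". The guideline goes out over the school intranet.

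The intervention side is described in four other sections.

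- Intervention Arm: the research team will hold a "briefing session and a demonstration session for all eligible students in participating schools in the intervention arm". In addition, "Campaign promotion brochures and posters will be distributed within those schools".
- Study Design: "Students in the intervention group will be given the opportunity to take part in the online quiz competition and refer others to join the campaign".
- Campaign Design: "The answer score and referral score will be summed into a total score that will be used for prize distribution". The competition runs for 30 days.
- Incentive Scheme: "The 10 highest scorers in each school will receive cash coupons of different values". Table 1 puts the total at HK$2500 for each school.

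**The concern.** The sentence on the contrast asserts a design property: that a difference between arms can be traced to how the information is presented. Matching the sources gives both arms similar access to information. It does not equalise contact with the research team, promotion inside the school, peer involvement or financial incentive, and each of these could plausibly move a self-reported attitude score.

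What is at stake is how a positive result may be read. The Abstract's conclusion speaks of an Internet-based intervention outperforming traditional health promotion. The Conclusion of the Discussion looks ahead to placing the online platform in the mainstream curriculum and adapting it to other topics, and it does not mention sessions, promotion or prizes. If the sentence on the contrast is taken at face value, a reader could carry the whole trial effect over to a platform run without those elements. If they are kept, their cost belongs in the cost-effectiveness argument.

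**Working it through.** The point is settled mainly by setting the two arms side by side.

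| Element | Intervention arm | Control arm as described |
|---|---|---|
| Information sources | Used to set the quiz questions | Listed in the electronic guideline |
| Format | Interactive quiz, correct answer shown after each choice | Printed leaflets and an electronic guideline, one-way |
| School sessions | Briefing and demonstration for all eligible students | None described |
| Promotion in school | Campaign brochures and posters | None described beyond the leaflets |
| Peer referral | Yes, with referral points | None described |
| Competition and coupons | Ranked on total campaign score | None described |

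Row 1 is matched and row 2 is the claimed contrast. Rows 3 to 6 also differ.

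**Which rows fall outside the claimed contrast.** The parenthesis in the sentence names a quiz competition. Rows 5 and 6 can therefore partly be read as inside it, because scoring, referral and prizes make up the competition. Rows 3 and 4 cannot: they are school-level activities that launch the campaign, described in a separate section. Rows 3 and 4 are enough to contradict the word ‘sole’. Rows 5 and 6 add to this if the contrast is taken to be interactive against one-way, since neither a cash coupon nor a referral point is a feature of interactivity.

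**Who can win coupons.** Incentive Scheme speaks of each school without naming an arm. Campaign Design ranks prizes on the sum of answer score and referral score, which only quiz participants have. Control students who join through a referral are to be excluded from the analysis (Control Arm section), so in the analysed data the coupons sit on the intervention side.

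**Prize total.** Inputs from Table 1: one prize of HK$500, two of HK$300 and seven of HK$200.

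- Per school: 1 × 500 + 2 × 300 + 7 × 200 = 500 + 600 + 1400 = HK$2500, for 1 + 2 + 7 = 10 prizes. This reproduces the stated total.
- With 20 schools (Abstract), half is 10: 10 × 2500 = HK$25,000.
- With 24 schools (Study Design), half is 12: 12 × 2500 = HK$30,000.

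These sums describe the incentive. They do not measure bias.

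**Sample size, as background.** A standardised difference of 0.5 with 80% power at .05 (two-sided assumed) needs 64 per arm, or 128. The design effect is 1 + (420 − 1) × 0.092 = 39.548, and 128 × 39.548 = 5062.1, in line with the stated figure of about 5063. Nothing in this point alters these figures.

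**The case against.** The strongest reply is that the sentence closes an argument about information content. In context it may mean only that information is matched and delivery differs, with delivery defined as the quiz competition. On that reading prizes, scoring and referral belong to the contrast. This stands in part, and it is why the sessions, brochures and posters carry the main weight here. It does not rescue the sentence, because those items are no part of the competition and are given to one arm only. It is fair to add that the brochures and posters advertise the campaign, with no alcohol-education content described for them, and that control students also receive printed leaflets.

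A second reply is that the objective is already set at the level of the package: the Objective in the Abstract and the end of the Introduction aim to test an online quiz competition, and Power Analysis compares the campaign with a traditional promotion strategy. This stands in full, and the objective needs no rewriting.

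A third reply is that an information package is a legitimate pragmatic comparator, and that no two-arm trial of a complex intervention separates its components. This also stands. The fault is that the article claims a separation which the design does not provide.

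A reader might go further and infer that the trial fails to test its own conclusion, or that the control arm must be matched for contact and incentive. The documents do not support either inference. The Abstract's conclusion concerns the intervention as a whole, no component or mediation analysis is promised, and the roll-out passage does not say that the platform would run without promotion or prizes.

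**Conclusion.** The sentence on the sole contrast is wrong as written, because the article's own description of the arms contradicts it. The sessions and school promotion clearly lie outside the stated contrast. Referral points and coupons lie outside it if the contrast is interactivity, and arguably inside it if the contrast is the whole competition.

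The trial can validly estimate the effect of the complete campaign against the information package. It cannot credit a difference to the interactive format alone, and the share of any effect due to the other components cannot be estimated from two arms. No figure in the article changes.

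Two assumptions are made: control schools receive nothing beyond what the Control Arm section describes, and schools are split equally, which gives 10 or 12 intervention schools depending on which school count is right. The prize total depends on that count; the conclusion does not.

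**What to change.** Replace the sentence in Control Arm: Information Package with wording such as: *The two arms draw on matched information sources. The trial compares the complete campaign (school sessions, promotion material, incentivised quiz and referral) with an information package, and cannot isolate the effect of the interactive format.*

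Word the Abstract's conclusion and the roll-out argument in the Discussion's Conclusion so that they apply to the whole campaign. Leave the objective as it is.

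This is a change of text only. Randomisation, outcomes and sample size stay as they are. The price is a narrower claim: a positive result would support the campaign as delivered, not the interactive format by itself.
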